## Background

Worldwide, running is a sport practiced by many individuals to improve cardio-respiratory function, health and well-being [1]. The Royal Dutch Athletics Federation (KNAU) has estimated that around 12.5% of all Dutch people are running on a regular basis, and that the popularity of running events is still growing. The popularity of running positively contributes to increasing levels of physical activity in the population. This is important, because physical inactivity is associated with the development of several chronic diseases, decreased longevity, loss of physical function and weight control [2]. Running is a feasible way for people to become more active. To start with running, just a pair of shoes is needed.

Although running positively contributes to health, there is also the possibility of a running related injury (RRI). The incidence of RRI's injuries in runners at recreational and competitive level is high and varies from 30% to 79% [3-9]. The wide range in incidence is caused by 1) differences in injury definition, 2) time of follow up, 3) differences in population at risk, and 4) differences in methods used to assess RRI, as well as exposure to running. Taking into account the exposure to running, an appropriate way to describe the incidence of RRI's is to calculate the number of RRI's per 1000 hours of running in the population at risk. Injury incidence per exposure varies from 7 to 59 per 1000 hours of running [3-5,10].

Most injuries in runners are overuse injuries of the lower extremity, caused by training errors, that is, running too much, too soon [11]. The exact cause and risk factors of RRI's are still unclear. However, it can be stated that the aetiology of these injuries is multifactorial and diverse. A review by Van Mechelen [12] proposed four factors that have been significantly related to running injuries: a) lack of running experience, b) previous injury, c) running to compete, and d) excessive weekly running distance.

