### Inclusion & exclusion criteria

Healthy participants between 18 and 65 years of age, who had no injury of the lower extremity in the three months prior to inclusion and who had not been running on a regular basis in the previous twelve months were eligible for inclusion in the study. Participants were excluded if there were absolute contraindications for vigorous physical activities according to the American College of Sports Medicine [25], or in case of unwillingness to keep a running log.

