### Sample size

A power calculation was carried out for the main outcome variable RRI, using a logistic rank survival power analyses. In other studies on novice runners incidence of RRI varies from 29.5 to 58% in a periods of respectively 13 to 28 weeks [3,8]. For the GRONORUN trial we expected an injury incidence of 30%. With a hypothesized 25% reduction of RRI's in the intervention group compared to the control group, a total of 436 runners (2 × 218) were needed for a power of 80% and an alpha of 0.05. The hypothesized reduction was based on clinical relevance, because no other studies on the prevention of RRI in novice runners were found. Assuming an attrition of 15% in the intervention period, a total of 512 (2 × 256) novice runners were needed to detect an effect of the intervention.

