### Baseline measurements

#### Questionnaire

The baseline questionnaire consisted of five parts and was sent back by mail in a pre-paid envelope before the initial appointment at the hospital.

Part one covered demographic variables such as name, address, age, gender, and e-mail address.

Information about medical history was collected by the second part of the questionnaire. Conditions related to risk factors for cardiovascular diseases were assessed using a series of questions according to the American College of Sports Medicine [25]. Questions about previous musculoskeletal complaints of the lower extremity and back were assessed per anatomical site. Open-ended questions were used to obtain information about body height (in cm) and body weight (in kg). These self-reported body height and weight data were used to calculate BMI (weight (kg)/height^2^(m)).

Sports participation was assessed in part three by using questions concerning type of sport and mean hours of sports participation. Furthermore, a question on running experience in the past ("Have you ever participated in running on a regular basis?") was used to assess the novelty to running.

Part four consisted of the Jenkins Activity Survey (JAS). The JAS is a tool to indicate type A behaviour [26]. Individuals with a pronounced type A behaviour, also referred to as coronary prone behaviour, are possibly more prone to injury [27]. Type A behaviour is characterized by above average achievement drive, aggressiveness, hostility, impatience, time urgency, and competitiveness [26].

Part five assessed the motivation for running, using a Dutch translated version of the Motivation Of Marathoners Scale (MOMS). The MOMS is an instrument that measures the motives of runners, by means of 56 items distributed across nine scales. Content areas covered include health orientation, weight concern, self-esteem, life meaning, psychological coping, affiliation, recognition, competition, and personal goal achievement. The MOMS was validated by Masters [28], and demonstrated an adequate internal consistency (Cronbach's alpha range .80 to .93), retest reliability (intraclass correlations range .71 to .90), and factorial validity of the scales.

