### Randomization

After baseline measurements and informed consent, participants were assigned to the intervention training program or the control training program. To ensure that both training groups were equal in terms of injury risk, a stratified randomization was performed. Participants were stratified for current sporting activities status, previous injury, and gender. Based on sporting activities, there are three categories of novice runners. The first category consists of novice runners who already are participating in a sport in which axial load (i.e., running, walking or jumping) is integrated. The second category is formed by novice runners who already are participating in sporting activities without axial load, like swimming and cycling. The third category is formed by novice runners who did not participate in any sporting activities at baseline measurements. In a study by Macera [6], a 74% increased risk was found in runners with a positive history of previous injuries. Since it is not clear whether the high rate of re-injury is caused by incomplete healing of a previous injury or a biomechanical problem, a differentiation in time is made. A distinction can be made between no previous injury, sustaining injured in the last 12 months before baseline measurements, and sustaining injured more than 12 months before baseline measurements. Eighteen strata were formed by gender, previous injury (no, 3–12 months and > 12 months) and sporting activities (no, with axial load and without axial load). From each stratum participants were allocated to intervention or control group by drawing a sealed opaque envelope. Each stratum box contained equal numbers of control and intervention envelopes.

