### Statistical analyses

To evaluate the success of the randomization, baseline values will be analyzed for differences between intervention group and control group, using a chi-square for categorical data and a student's t-test for numerical data. To analyze the primary outcome (i.e., RRI), the Kaplan-Meier method will be used. Once a participant has a RRI his or her survival time will be terminated. To evaluate the effect of the intervention, a log rank test will be used to compare the Kaplan-Meier curves of the intervention group to the control group. Analyses will be performed following the "intention to treat" principle. Differences will be considered statistically significant at p < 0.05. All analyses will be done using SPSS version 12 (SPSS, Chicago, Illinois).

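### The intervention is tested with an unadjusted log-rank test that leaves out both the randomisation factors and injury predictors measured at baseline: a valid test, but a modest and cheaply avoided loss of efficiency

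*Protocol article*

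**What the plan says.** The Statistical analyses section of the protocol article describes Kaplan-Meier curves for time to first running related injury (RRI), and then "a log rank test will be used to compare the Kaplan-Meier curves of the intervention group to the control group". The analysis follows intention to treat, and "Differences will be considered statistically significant at p < 0.05". No covariate or stratum is named. The same section plans chi-square and t-tests of baseline values between arms and does not say what follows if one is significant.

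The Background reports "four factors that have been significantly related to running injuries: a) lack of running experience, b) previous injury, c) running to compete" and, as the fourth, excessive weekly distance. The Discussion again calls lack of running experience a risk factor. Under Questionnaire, the baseline form includes "a question on running experience in the past", a motivation scale (MOMS) with a competition subscale, and a type A survey, included because "Individuals with a pronounced type A behaviour, also referred to as coronary prone behaviour, are possibly more prone to injury".

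Under Randomization, "Participants were stratified for current sporting activities status, previous injury, and gender", giving 18 strata. Eligibility admits people "who had not been running on a regular basis in the previous twelve months", so lapsed regular runners can enter alongside people who have never run.

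**The concern.** The plan treats injury risk as something to equalise between the arms and collects several variables because they may predict injury. It then fixes an effect analysis that uses none of them. In time-to-event data, leaving out strong predictors moves the estimated hazard ratio toward 1 relative to the conditional one and costs some power.

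There is also a procedural gap. If a baseline test flags an imbalance in, say, past running experience, the team must either ignore it or adjust after seeing the data. The plan does not say which. A covariate list fixed in advance closes that choice, whatever the power gain.

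**Working it through.** **1. The passages side by side**

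| Factor | Linked to injury in | Measured at baseline | Stratified | In the test |
|---|---|---|---|---|
| Past running experience | Background, Discussion | Yes (yes/no question) | No | No |
| Running to compete | Background | By proxy (MOMS competition motive) | No | No |
| Type A behaviour | Questionnaire, as a possibility | Yes | No | No |
| Previous injury | Background, Randomization (74% higher risk) | Yes | Yes | No |
| Gender, sporting activity | Randomization | Yes | Yes | No |

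Weekly distance is largely set by the allocated programme, so it is not a candidate covariate.

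**2. The plan's own figure**

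The Sample size section says that "a total of 436 runners (2 × 218) were needed for a power of 80% and an alpha of 0.05", from 30% incidence and a 25% reduction. Read as a relative reduction, this is 30% v 22.5%:

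- HR = ln(0.775)/ln(0.70) = 0.715; log HR = -0.336.
- Two-sided Schoenfeld calculation: 279 events. Mean event rate (0.30 + 0.225)/2 = 0.2625, so N = 279/0.2625 = about 1063.
- Power with 218 per arm: about 43 to 44%. With 266 per arm: about 51%.

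The stated 436 is not reproduced. That is a separate matter; here it only sets the baseline from which any gain is counted. The attrition step does agree: 436/0.85 = 513 against 512 stated.

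**3. Power gained by adjustment**

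The article gives no effect size for the three unstratified variables, so strengths are assumed over a range. Arm risks are held at 30% and 22.5%.

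*218 per arm, three independent binary covariates at 50% prevalence, 6,000 trials per row (standard error about 0.6 points):*

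| HR per covariate | Log-rank | Stratified log-rank | Adjusted Cox | Gain (Cox) |
|---|---|---|---|---|
| 1.3 | 43.6% | 43.7% | 43.5% | -0.1 |
| 1.74 | 43.8% | 44.8% | 45.2% | 1.4 |
| 2.5 | 42.5% | 49.4% | 50.2% | 7.7 |

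*264 v 268, one binary covariate (never-runner, 50%) and two continuous ones (competition, type A; HR per SD), 3,000 trials per row:*

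| HRs | Unadjusted | Adjusted |
|---|---|---|
| 1.3, 1.15, 1.1 | about 50% | about 51% |
| 1.74, 1.3, 1.2 | about 49% | about 51% |
| 2.0, 1.6, 1.4 | about 51% | about 56% |

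The value 1.74 is borrowed from the article's figure for previous injury and is not evidence about the other variables. The randomisation factors were not simulated separately.

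**4. Where the gain comes from**

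In the 218-per-arm runs the standard error of the log HR is 0.190 unadjusted and 0.191 adjusted. The log HR moves from -0.341 to -0.353 (HR 1.74 each) and from -0.338 to -0.372 (HR 2.5 each).

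**5. Validity**

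With no treatment effect and covariates at HR 2.5, 9,000 trials give a type I error of 4.9% for the plain log-rank test and 5.3% for the adjusted Cox model.

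**6. Chance imbalance in one realised sample**

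- SD of the between-arm difference for a 50% characteristic: sqrt(0.25 × (1/264 + 1/268)) = 0.0434.
- A 2-SD imbalance is 0.0867. With HR 1.74 it shifts the log HR by 0.0867 × ln(1.74) = 0.048.
- Expected first injuries: 264 × 0.225 + 268 × 0.30 = about 140. SE = sqrt(4/140) = 0.17.
- Shift/SE = 0.048/0.17 = about 0.28. As a share of the planned effect: 0.048/0.336 = 14%.

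**7. Is the model affordable?**

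Treatment 1, gender 1, sporting activity 2, previous injury 2, past running 1, competition 1: 8 parameters, or 140/8 = 17.5 injuries each. With type A, 140/9 = 15.6. If the 15% attrition removed events in proportion, 140 × 0.85 = 119, or 14.9 and 13.2.

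**The case against.** The strongest reply is that nothing here is wrong. Under randomisation and intention to treat, an unadjusted log-rank test holds its error rate, and chance imbalance in unstratified predictors is already part of that error rate. The simulation bears this out, and the reply stands.

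It is also fair that the predictors are thinly supported. Type A is only a possibility, the MOMS scale measures a motive, the eligibility rule narrows the contrast in experience, and the Background's list concerns runners in general. At weak to moderate strengths the gain is close to nothing. A 2-SD imbalance should occur in only about 5% of trials for any one factor, and it moves the estimate by little more than a quarter of a standard error.

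A supporting adjusted model, or a hazard ratio with an interval, may also sit in an analysis plan that is not shown, so their absence from the article is not itself a fault.

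What survives is narrower. The article does state how the effect will be evaluated. That choice leaves out the randomisation factors and predictors already collected, and the baseline tests have no stated consequence.

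**Conclusion.** This is a minor point: a valid analysis that could be made slightly better at almost no cost. Adjustment would add about 0 to 2 points of power if the predictors are weak to moderate, and about 5 to 8 if they are strong. These figures rest on assumed hazard ratios, prevalences and independence between covariates; the article supplies none of them for the unstratified variables.

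A reader might infer three stronger things, none of which the document supports:

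- *That the result would be biased or the test invalid.* The type I error is nominal. The unadjusted mean log HR of about -0.34 matches the planned marginal value of -0.336. The larger adjusted value is a conditional effect, not a correction of bias.
- *That precision is thrown away.* The standard error does not fall with adjustment.
- *That adjustment would rescue the trial's power.* From about 43 to 51% unadjusted, even the strong scenarios reach only about 50 to 56%.

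**What to change.** Before outcome data are viewed, add to the Statistical analyses section a Cox model for time to first RRI with a fixed covariate list:

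- the randomisation factors: gender, sporting activity (three levels) and previous injury (three levels);
- previous regular running (yes/no) and MOMS competition score;
- type A score if wanted, with that decision made now.

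Leave out any term whose inclusion depends on the event count. Report the adjusted hazard ratio with its 95% confidence interval alongside the Kaplan-Meier curves and the unadjusted log-rank test. Name in advance which of the two carries the conclusion: the small power gain is obtained only if it is the adjusted model. State that the baseline significance tests will not decide what is adjusted for.

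The cost is a few sentences and one model, with no new data or participants. Two downsides should be stated. The adjusted hazard ratio is conditional and will differ somewhat from the unadjusted one. The model also assumes proportional hazards between an 8-week and a 13-week programme with different load profiles; a check of that assumption should be planned.

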## Discussion

The GRONORUN trial is the first randomized controlled trial to study the effect of a modification of a training program on RRI's in novice runners. There is a need for well controlled trials about preventive interventions in running populations because of the popularity of running and the high rates of RRI's.

Novice runners are often physically inactive before they start to run. The health benefits in this previously physically inactive group can be high. On the other hand, lack of running experience is one of the risk factors for a RRI [6]. The major reason for discontinuation (drop out) of a running program is injury [33]. Negative experiences, caused by an injury that occurs while training for a running event, have the potential to significantly affect the future physical activity of each individual [34]. It is also known that (fear of) sustaining an injury is associated with failure to start and maintain a physically active lifestyle [34]. So, prevention of injuries in novice runners is important.

On the internet and in running shops different training programs for novice runners are available. Most of the programs are based on expert opinion. There are numerous "experts" and they all have their own opinion of "the best running program", however none of them are based on scientific evidence.

As a result of the GRONORUN trial, valuable information will be gained on training programs for novice runners. With this new information on training programs, it might be possible to reduce the incidence of RRI's in future.
